### Inclusion and exclusion criteria

#### Patients

Inclusion criteria require patients: 1) to be primarily diagnosed with a social anxiety disorder (SCID [50]; corresponding ICD diagnosis: F40.1); 2) to have a LSAS-SR total score >30; 3) to be on stable medication for at least 4 weeks, in cases of concurrent pharmaceutical treatment; 4) to agree to participate in the pilot study and to be randomized into one of the study arms; 5) to agree to not use additional therapeutic support during the study period; and 6) to be 18–65 years old. Exclusion criteria are as follows: 1) acute substance dependency; 2) psychotic disorders; 3) eating disorders (BMI <14); 4) severe physical diseases; 5) acute suicidality; 6) insufficient German language skills; and 7) private health insurance and participation in psychotherapy financed by the national health insurance companies within the past year due to administrative regulations at one of the centers. Comorbid disorders are allowed as long as the social anxiety disorder is of primary concern.

#### Therapists

Inclusion criteria required therapists: 1) to be advanced trainees with more than 300 hours of theoretical and clinical training; 2) to have therapeutic self-experience of at least 100 hours; 3) to have completed an internship in psychosomatic medicine, psychotherapy or psychiatry of at least 600 hours; and 4) to participate in the CBT or ST training and supervisions. If therapists have training in both approaches, they will be assigned to the approach that they consider their primary therapeutic identity. We will choose advanced trainees due to their strong treatment adherence and ability to deliver treatments effectively in outpatient settings [51].

### Randomization

Following inclusion, patients will be randomized, using block randomization in a 1:1 ratio to obtain equal group sizes [52]. We will use a randomization plan generator (www.randomization.com). An independent research team will conduct the assignment of patients to study arms. Therapists will be randomly assigned to patients as they enter the project.

### Blinding and allegiance

#### Blinding

Patients will be informed about their assignment (no blinding, open trial), the general study aims and procedures, but not about specific hypotheses. Blinding will not be feasible since both the CPP and IMP are well known for their specific therapy orientation, and because of the focus on the external validity and generality of the pilot study to routine care [53]. Outcome assessments at all points in time will be conducted online (UNIPARK), and no blinding of assessors will be needed. Pre- and post-SCID diagnostics will be blinded and the assessors will not know the study arm in which each patient will be treated.

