### Study procedures

#### Screening and diagnostic process

Interested individuals will initially take part in a telephone screening assessment of the main socially anxious symptoms (SCID, social anxiety disorder). Persons meeting the inclusion criteria will then receive the LSAS-SR self-report measure and SCID screening questionnaires together with the study information, informed consent and declaration about the DVD record use by post. After signing and sending back these documents, the documentation will be checked and the LSAS-SR score will be calculated and analyzed. If all documents are signed and the interested person shows a LSAS-SR >30, then the individual will be invited to a SCID-I and -II face-to-face interview, including the assessment of the general level of functioning (Global Assessment of Functioning; GAF). These pre-SCID interviews will be rated by independent raters with respect to both primary and secondary diagnoses. After inclusion based on shared decision making by clinical experts in the bi-centric case conference, persons will be randomized. Subsequently, they will be informed whether they will be treated in the CBT or ST study arm. Individuals will then attend a social network interview. In this interview they will select a significant other (e.g. partner, family member, best friend) who will then be asked to fill in a questionnaire booklet assessing significant others' burden.

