##### Therapy (T1 to T5)

We will assess study outcomes before the start of therapy, after the 8th, 15th and 20th hour of therapy, as well as after therapy has ended. At each time of assessment, patients will participate in an online survey (UNIPARK) including study outcomes (Table 1). The assessment will be conducted at the IMP. Baseline data (T1) will be scheduled no more than 5 days before the first therapy session. Therapy process (T2 to T4) will be assessed no more than 5 days after the 8th, 15th and 20th hour of therapy. The primary endpoint (T5) will be defined by a joint patient-therapist decision to end therapy or by the end of 26 hours of therapy. All outcome variables will be assessed anew, along with in- and outpatient health care service data. A post-SCID and social network interview will also be conducted. Like the pre-SCID, the post-SCID interviews will be rated by independent raters considering primary and secondary diagnoses.

**Table 1 Tab1:** Assessment measures and application plan

Purpose	Perspective	Domain	Instrument	Screening	Baseline	8th, 15th, 20th hour of therapy	End of therapy, no later than 26th hour of therapy	9 and 12 months after beginning of therapy
					T1	T2 to T4	T5	T6 and T7
Screening	Pat	Social anxiety	LSAS-SR	X				
	Diag	Mental disorder SAD	SCID: SAD	X				
Outcome	Diag	Mental disorders	SCID I, II	X			X	
	Pat	Social anxiety	LSAS-SR	X	X	X	X	X
	Pat	Social anxiety	SIAS	X	X	X	X	X
	Pat	Social anxiety	SPS	X	X	X	X	X
	Diag	Global functioning	GAF	X	X		X	
	Pat	Depression	BDI-II	X	X	X	X	X
	Pat, Ref	General symptom severity	BSI	X	X	X	X	X
	Pat, Ref	Experience of social systems	EXIS	X	X	X	X	X
	Pat, Ref	Evaluation of social systems	EVOS	X	X	X	X	X
	Pat, Ref	Dyadic adjustment	DAS-12	X	X	X	X	X
	Pat	Interpersonal problems	IIP-32	X	X	X	X	X
	Pat, Ref	Symptom adjustment	ASS	X	X	X	X	X
	Ref	Burden	BAS		X	X	X	X
Process	Pat, T	Therapeutic alliance	SACiP			X	X	X
	Pat, T	Therapeutic relationship	SRS			X	X	X
	Pat	Therapy motivation	URICA			X	X	X
	Pat, T	Credibility	OAT		X			
Therapists	T	Common therapist factors	DPCCQ		X	X	X	X
Quality	R	Adherence and competence	STAS, CTAS-SP		X	X	X	X
Additional service	Pat	Service receipt	CSSRI-EU				X	X

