##### Secondary outcome measures: psychological functioning

The GAF scale measures clinicians’ evaluation of patients’ psychosocial functioning [62, 63] with high levels of interrater reliability [64] and sensitivity to change [62]. The 21-item Beck Depression Inventory II (BDI-II) detects cognitive, motivational, affective and somatic symptoms of depression with excellent to good internal consistencies [65, 66] and high sensitivity to change [67]. The Brief Symptom Inventory (BSI) assesses a variety of mental symptoms, and is highly correlated to the original SCL-90-R [68–70].

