#### Mixed-design ANOVA

We will perform mixed-design ANOVA to identify differences between treatment conditions [95]. Factors will be group (CBT or ST) and time (baseline, 8th, 15th, 20th therapy hour, end of therapy, respectively 26th therapy hour, 9 and 12 months after the beginning of therapy). Contrasts A will compare baseline with end of therapy. Contrasts B will indicate change between end of therapy, respectively 26th therapy hour, and 9 months after the beginning of therapy. Contrasts C will indicate change between end of therapy and 12 months after the beginning of therapy. We will control for differences in the length of treatment.

Time X Group interaction effect sizes will be assessed with partial eta-squared (η^2^) for the mixed-design ANOVA. Classification of effect sizes will be: η^2^ ≥ 0.01, small effect; η^2^ ≥ 0.06, medium effect; and η^2^ ≥ 0.14, large effect. Subsequently, for significant Time X Group interactions, simple effect analyses within and between groups will be performed [96]. Between-group effect sizes will be assessed with η^2^ and Cohen’s *d*. Classification of Cohen’s *d* will be: *d* ≥0.20, small effect; *d* ≥0.50, medium effect; and *d* ≥0.80, large effect [34]. In accordance with Coe [97], we will interpret Cohen’s *d* in terms of percentiles. Within-group effect sizes will be assessed with η^2^.

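### The claim that all outcomes are online and need no assessor blinding is wrong for the clinician-rated GAF, and the GAF marked at T1 has no described rating contact

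*Protocol article*

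**What the plan says.** The Blinding section gives one rule for outcomes: "Outcome assessments at all points in time will be conducted online (UNIPARK), and no blinding of assessors will be needed". The next sentence gives another for the diagnostic interviews: "Pre- and post-SCID diagnostics will be blinded and the assessors will not know the study arm in which each patient will be treated".

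The GAF is listed under "Secondary outcome measures: psychological functioning" and described this way: "The GAF scale measures clinicians’ evaluation of patients’ psychosocial functioning". Table 1 assigns it to the diagnostician at screening, T1 and T5.

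Screening and diagnostic process places the first GAF in the face-to-face SCID-I and -II interview, "including the assessment of the general level of functioning (Global Assessment of Functioning; GAF"). That interview precedes the case conference, randomization and disclosure of the arm.

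For T1 to T5 the text describes a patient survey: "At each time of assessment, patients will participate in an online survey (UNIPARK) including study outcomes (Table 1"). A post-SCID interview is added at the end of therapy. In the Mixed-design ANOVA section, "Contrasts A will compare baseline with end of therapy".

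**The concern.** The reason given for not blinding assessors is that outcomes are entered online. That reason fits the questionnaires. It does not fit a scale that a clinician scores face to face. Taken literally, the sentence covers the GAF and excuses its rater from blinding. The following sentence points the other way but names only SCID diagnostics.

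The schedule adds a second difficulty. T1 falls within five days of the first session and, in the order the text describes, after patients have been told their arm. Table 1 puts a diagnostician-rated GAF there but no SCID, and the text describes only a patient survey.

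The GAF is the only scale among the outcome rows of Table 1 that is rated by a diagnostician rather than by the patient or reference person. In an open trial it is therefore the one scaled measure of psychological functioning (H2) that could be kept free of the patient's knowledge of the arm. Its value for that purpose depends on the rater being blinded and on a baseline of known origin.

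**Working it through.** This point involves no figure of the plan to reproduce. The check sets the sections side by side.

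**1. Is the online statement true of every outcome?** Table 1 has 13 outcome rows. Eleven are rated by the patient, the reference person or both: LSAS-SR, SIAS, SPS, BDI-II, BSI, EXIS, EVOS, DAS-12, IIP-32, ASS and BAS. Two are rated by the diagnostician: SCID I/II and GAF. The Blinding section makes an exception for the SCID. It makes none by name for the GAF, so as worded the statement is wrong for that scale.

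**2. What covers each GAF rating?**

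| GAF mark in Table 1 | SCID at the same time? | Contact described in the text | Patient knows the arm? | Blinding text |
|---|---|---|---|---|
| Screening | Yes | SCID face-to-face interview, GAF named | No, before randomization | Not at issue |
| T1 | No | Patient online survey only | Yes, by the order of the text | None |
| T5 | Yes | Post-SCID interview, GAF not named | Yes | SCID assessors blinded, GAF not named |

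**3. Do the SCID safeguards reach the GAF at T5?** Three places describe independent rating of the interviews: Screening and diagnostic process, Therapy (T1 to T5), and Interrater reliability. The first two limit it to primary and secondary diagnoses. The third covers SCID diagnoses and treatment adherence. The GAF is in none of them. Table 1 pairs GAF and SCID at T5 with the same type of rater, and the pre-treatment GAF is part of the SCID interview. The natural inference is that the T5 GAF is scored by the blinded post-SCID assessor, but this remains an inference.

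**4. What could the T1 mark mean?** There are three readings.
- It may be the pre-SCID rating under another label. Interrater reliability calls the pre-therapy SCID T1 and the end-of-therapy SCID T2, which Table 1 calls T5, so labels do drift. Against this, the GAF already has its own screening mark, and the SCID row has no T1 mark.
- It may be a second diagnostician rating after allocation, for which no contact, rater or blinding is described.
- It may be a mark with no rating behind it.

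The document does not decide between them.

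**5. Does it matter for the analysis?** The GAF is not scheduled at T2 to T4, T6 or T7. Contrasts B and C need the 9- and 12-month values, so only Contrast A fits the GAF. It starts at baseline, the label Table 1 gives to T1. Read literally, the only GAF contrast uses the undescribed rating instead of the documented pre-randomization one.

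**6. Can a size be given?** With 16 per arm, the standard error of a standardized mean difference is √(1/16 + 1/16) = √(2/16) = 0.354 SD. A rater bias of b SD would be b/0.354 standard errors. The document gives neither a GAF standard deviation nor any value for b, so no bias can be derived.

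**The case against.** The strongest reply is that the protection stands in the very next sentence. SCID assessors are blinded to arm, the GAF is part of the SCID interview at screening, and Table 1 schedules the two together at T5. On that reading the first GAF precedes randomization and the last is blinded. A condensed article may leave the rest to the full protocol.

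This largely stands. A reader might infer that the GAF is left open to assessor bias. The document does not support that: no section has the T5 rater unblinded, and arm knowledge cannot affect a rating made before randomization. For the same reason it cannot be said that all 32 patients have a compromised rating. An assumed bias of 0.2 to 0.4 SD would be 0.2/0.354 = 0.57 to 0.4/0.354 = 1.13 standard errors, but nothing in the document supports that range. Setting it against the 0.3 SD in Design and sample size would also mislead, because that figure comes from a cited methods paper on main-trial size and is not a GAF threshold.

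A reader might also infer two competing baselines, or a visit at which diagnosticians learn the arm. Only T1 is labelled baseline, ten patient-reported scales carry the same double mark, and no such visit is described. The screening column is loose elsewhere too: it marks scales with a reference-person perspective, although that person is chosen only after randomization.

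Two things survive. The online sentence is wrong for the GAF and is not an omission left to a fuller document. The T1 GAF also differs from the ten double-marked scales: their T1 value comes from the online survey, and the GAF's comes from no contact the text describes.

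**Conclusion.** The point holds as a minor correction. The online, no-blinding statement is wrong for one diagnostician-rated secondary outcome. Blinding of the T5 GAF is probable but not stated. The T1 GAF mark is unexplained, may be a labelling error, and is nominally the start of the only planned contrast the GAF can enter.

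The conclusion rests on reading Table 1's diagnostician label as the rater of the GAF, which the description of the scale confirms, and on taking T1 to follow disclosure of the arm, as the order of the text implies. It does not rest on any assumed bias, and none can be calculated. The primary outcomes (LSAS-SR, SIAS, SPS) are self-reported and unaffected, all analyses are exploratory, and no figure in the plan changes.

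**What to change.** - **Blinding:** limit the online, no-blinding sentence to self-report measures, and state that both SCID and GAF are rated by assessors blinded to arm.
- **Therapy (T1 to T5):** state that the T5 GAF is rated in the post-SCID interview by that blinded assessor.
- **Table 1:** remove the GAF mark at T1, and define the GAF baseline as the rating from the pre-randomization SCID interview.
- **Mixed-design ANOVA:** for the GAF, compare end-of-therapy scores between arms, adjusted for the pre-randomization rating. The adjustment is an analysis choice separate from blinding, and the other three changes stand without it.
- **Interrater reliability:** align the time labels with Table 1, so that the pre-therapy and end-of-therapy SCID are not called T1 and T2.

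The cost is a few sentences and one table cell. No visit or staff is added, because the SCID interviews already take place. The small downside is a longer gap between the baseline GAF and the start of therapy.

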#### Allegiance

The preference of researchers and therapists for a particular treatment may account for bias in outcome data [54]. To avoid such bias, we will balance direct and indirect allegiance by a bi-centric trail. In this trail, CBT and ST trainers, supervisors and therapists will be distinct persons but equally allegiant to their method. They will be well trained, follow equally elaborate but quite distinctive manuals. They will receive equal support, and contribute an equal number of hours and days to the project [55].

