### Ethical consideration

CBT will be practiced at the Center for Psychological Psychotherapy (CPP), Heidelberg University, and ST at the Institute of Medical Psychology (IMP), Heidelberg University Hospital. All therapies will be recorded. The pilot study design, the measurement times and instruments are aligned with the studies of Willutzki and colleagues [5], Rakowska and the SOPHO-NET [48]. This research was approved by the Ethics Committee of the Heidelberg Medical Faculty (S-190/2014). Written informed consent will be obtained from each interested person. Staff will send the study information, informed consent and declaration about the usage of DVD records to each interested person after the initial telephone interview. The staff will be available for any questions on the telephone or face-to-face at the IMP during workdays. All interested persons will be informed about their rights to end their participation at any time without negative consequences. Confidentiality will be maintained at all levels of the pilot study by staff members, diagnosticians, therapists, supervisors and researchers. All of them have to declare bindingly that they will give no information to third persons. Additionally, we will work with identification codes for each interested person and patient. All data will be saved pseudonymized on the IMP server. This pilot trial will be conducted in accordance with the Declaration of Helsinki [49], as well as with the State Chamber of Physicians of Baden-Wuerttemberg, Germany.

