#### Clustering effects

CBT and ST will be administered in two independent centers. There will be considerable interaction among the therapists within each study arm, particularly during training and supervision. Within the ST condition, there will also be interaction between patients, above all in the group therapy session. Due to data dependency, we will conduct two-level (patients, treatment condition) linear regression analysis to account for positive intra-class correlations (ICCs) with respect to the primary outcome measures [91, 92].

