### Biases and limitations

This trial is a pilot study and all statistical analyses will be descriptive and explorative, with the aim to obtain data that can then be used for planning a confirmatory RCT. Consequently, the main RCT is necessary before any confirmatory statement about the efficacy of ST for social anxiety disorders can reliably be made. It is also an open study, and patients and therapists will be informed about the study arm to which they will be allocated. Patients will present themselves to the study team, and no patient will be referred. The openness of this trial and type of recruitment is a naturalistic fact of “real world delivery of care” ([53]; p. 6). We try to balance direct and indirect allegiance by conducting a bi-centric trial, involving equally experienced ST and CBT experts, and implementing high methodological quality that appears to buffer allegiance [55]. The additional use of the OAT questionnaire [84] will help to test if we could balance allegiance. However, due to the small sample size, we will not perfectly control for allegiance effects.

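### Arm and centre coincide (CBT only at the CPP, ST only at the IMP), so the bi-centric design cannot ensure or show that allegiance bias is avoided

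*Protocol article*

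**What the plan says.** The Allegiance section of the protocol article names the preferences of researchers and therapists as a source of bias and gives the remedy: "To avoid such bias, we will balance direct and indirect allegiance by a bi-centric trail". It explains that "CBT and ST trainers, supervisors and therapists will be distinct persons but equally allegiant to their method", and adds: "They will receive equal support, and contribute an equal number of hours and days to the project".

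The layout of the two centres is stated elsewhere. Ethical consideration has: "CBT will be practiced at the Center for Psychological Psychotherapy (CPP), Heidelberg University, and ST at the Institute of Medical Psychology (IMP"). Clustering effects has: "CBT and ST will be administered in two independent centers". Because of dependency within arms, the same section says "we will conduct two-level (patients, treatment condition) linear regression analysis to account for positive intra-class correlations (ICCs"). The Blinding section notes that "both the CPP and IMP are well known for their specific therapy orientation".

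Biases and limitations is softer. It presents the balance as something attempted, says "The additional use of the OAT questionnaire [84] will help to test if we could balance allegiance", and concedes imperfect control of allegiance, giving the small sample as the reason. The Credibility section describes the OAT as a measure of patients' expectation of benefit, with a therapist version to be adapted.

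**The concern.** A two-centre trial can offset centre differences when both treatments are given at both centres, because each centre then supplies its own comparison. Here each centre supplies one arm. Whatever distinguishes the CPP from the IMP, including how strongly each team believes in its method, goes into the CBT-minus-ST difference. The Allegiance section presents the design as avoiding this bias, and the limitations section implies that a larger sample would bring it under control.

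The effect size is the main product of the pilot. The Hypotheses section says it will be used to calculate how many patients are needed to replicate the effect, and the planned confirmatory trial is multi-centric. An effect specific to two teams, read as the effect of therapy, would carry over into that calculation.

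**Working it through.** **The protocol's own figures.** Design and sample size gives 350 for a 0.3 SD difference (80% power, two-sided 5%) and 32 for the pilot. Both reproduce:
- Main trial, per arm: 2 × (1.960 + 0.842)² / 0.3² = 174.4, rounded up to 175, so 350 in total.
- Pilot, per arm, one-sided 80% limit: 2 × (0.842 / 0.3)² = 15.74, rounded up to 16, so 32 in total.

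The sizing arithmetic is not in question. It contains no term for centre.

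**Can centre be estimated?** Code arm as 0 for 16 CBT patients and 1 for 16 ST patients, and code centre in the same way (CPP 0, IMP 1). The columns are identical (correlation 1), and the design matrix [1, arm, centre] has rank 2 of 3. The estimable quantity is therapy effect plus centre effect, and nothing in the data divides it. For contrast, with 8 patients per arm at each centre the correlation is 0, the rank is 3, and the variance of the arm effect is unchanged at 0.125 SD² (2/16).

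**Can the two-level model help?** Its upper level is treatment condition, which has two units. After the intercept and the treatment effect are fitted, 2 − 2 = 0 degrees of freedom remain for between-unit variance. The ICC it is meant to account for cannot be estimated separately from the contrast of interest.

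**Does a larger sample help?** Suppose there is no therapy difference but a pure centre effect δ (assumed values). The contrast is biased by δ at every N. By the normal approximation with SE = √(2/n), the two-sided 5% false-positive rate is:

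| δ (SD) | 16 per arm | 175 per arm |
|---|---|---|
| 0.1 | 5.9% | 15.5% |
| 0.2 | 8.7% | 46.5% |
| 0.3 | 13.6% | 80.1% |
| 0.5 | 29.3% | 99.7% |

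The last column keeps the one-centre-per-arm layout. It shows that sample size is not the remedy and does not predict the multi-centric main trial.

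**How much wider would an interval be?** The patient-level SE is √(2/16) = 0.354 SD, giving a 95% half-width of 1.96 × 0.354 = 0.69 (about 0.72 with the t quantile on 30 df). With an assumed centre ICC, the centre difference has variance 2 × ICC/(1 − ICC) in within-centre SD units, and the half-width is 1.96 × √(0.125 + 2 × ICC/(1 − ICC)):

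| Assumed ICC | SD of centre difference | Half-width |
|---|---|---|
| 0.01 | 0.14 | 0.75 |
| 0.02 | 0.20 | 0.80 |
| 0.05 | 0.32 | 0.94 |
| 0.10 | 0.47 | 1.15 |

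Scaling to total variance instead gives variances of 2 × (ICC + (1 − ICC)/16), which are 0.14375 at ICC 0.01 and 0.3125 at 0.10, and so half-widths of 0.74 to 1.10.

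**What this could mean for sizing.** Suppose the package difference is 0.3 SD and an assumed 0.1 SD of it is centre. The therapy part is 0.2 SD, and 2 × (1.960 + 0.842)² / 0.2² rounds up to 393 per arm, or 786 in total, against 350. If the centre effect works the other way, the therapy part is 0.4 SD and the formula gives 99 per arm, or 198 in total.

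**The case against.** The strongest reply is that the protocol claims balance of allegiance and not of centre effects, and that it says how: separate teams committed to their own method, comparably elaborate manuals, equal support and time. One team per therapy is how such balance is arranged, and it does avoid a team loyal to one method delivering both. This stands. A reader might infer from the confounding that the claimed balance does not exist. The documents do not support that: the teams may well be equally committed. What fails is the further step that bias is thereby avoided, because equal commitment is assumed and cannot be distinguished from other differences between the centres.

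A reader might also infer that people from outside handle CBT while the authors of the ST manual handle ST. The second half is documented: those authors ran the ST workshops and one of them supervises. The first half is not. Training and supervision places the CBT supervisors at the CPP itself, and only the CBT workshop leader comes from another university.

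Nor does any section say that a non-significant OAT difference would be taken as proof of balance. The objection to the OAT is narrower: it measures expectancy, so even a precise result would not test the allegiance of researchers and therapists, though the therapist version comes closer.

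Other points reduce the weight. Patients come from one recruitment effort, are screened jointly and are randomized individually, so case mix should not differ systematically and only delivery-related effects remain. Both arms complete the same online self-reports. Clustering effects and the Discussion disclose much of the separation between the arms, and the analyses are declared exploratory. None of this makes the effects separable, and no section states that centre and therapy are confounded.

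**Conclusion.** The point holds as a limit on what the design can deliver. Arm is fully confounded with centre, therapist pool, trainers and supervisors. The bi-centric layout therefore cannot ensure or show that allegiance bias is avoided, and the two-level model cannot repair this. Attributing the imperfect control to sample size alone is wrong, because the bias stays the same at any N.

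These conclusions follow from the stated layout and need no assumed value. The size of the effect is unknown. The false-positive rates, the half-widths of about 0.75 to 1.15 SD and the sizing examples all rest on assumed centre effects or ICCs, and they are illustrations, not estimates of the true error. Comparing each therapy as delivered by its own team remains a legitimate pilot target, provided it is named as such.

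**What to change.** 1. In Allegiance and in Biases and limitations, replace the claim that the bi-centric design balances allegiance. State that the contrast is CBT as delivered at the CPP versus ST as delivered at the IMP, and that centre and team effects cannot be separated from therapy. Say that this is structural and not only a matter of sample size.
2. In Clustering effects, do not present the two-level model as a correction for this confounding.
3. Report the OAT arm difference, in the patient and therapist versions, with its interval, as a description of expectancy and not as a test of allegiance balance.
4. When the pilot estimate is used to size the multi-centre main trial, treat it as a package effect and show its sensitivity over a range of centre effects labelled as assumed.

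The cost is rewording and one small table, with no change in trial conduct. The downside is a weaker stated conclusion.
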